#### Midwife-assisted RM group

Pregnant women allocated to the midwife-assisted RM group will also receive a blood pressure monitor, as used in the PSM group, and will be asked to measure their blood pressure twice daily. They will also register their body weight every week in the app. The data will be sent to the hospital for review by the allocated midwife. The midwife will contact the responsible obstetrician if any abnormal values are detected allowing interventions to be performed if necessary, or when the pregnant woman doesn’t take her vital parameters for more than 48 h. This study group is identical to that in PREMOM I.

#### Subgroup randomization

The women in all three study groups will be randomized in two subgroups at a 1:1 ratio, as follows.
Subgroup 1, medication adjustment: If an increase in blood pressure is detected, the woman’s cardiovascular profile will be measured using a hemodynamic monitor (USCOM 1A Uscom, Sydney, Australia). Based on the results, adjusted antihypertensive medications will be given to the woman.Subgroup 2, no medication adjustment: when an elevation of the blood pressure happens, the cardiovascular profile will not be measured. The pregnant woman receives the medication following the local obstetrician’s standard procedures.

In total are there six study groups into which the pregnant women can be divided.

### Treatment of pregnant woman

All pregnant women in each group are started on aspirin (Asaflow©), 160 mg once daily, consistent with the latest scientific evidence (e.g., from the Aspirin for Evidence-based Pre-eclampsia Prevention Trial [29]) concerning the follow-up of pregnant women at increased risk of developing PE. Pregnant women allocated to the ‘adjusted medication subgroup’ will be treated according to the cardiac output measured using a USCOM 1A monitor once blood pressure problems are detected. Cardiac output shows three presentations, each of which involves different treatments selected based on recent publications [30–39]. Women with low cardiac output will receive a calcium blocker, women with a normal cardiac output will receive α-methyldopa, and women with high cardiac output will receive a β-blockers. The reference values are shown in Table 1 [40].

**Table 1 Tab1:** Normal cardiac output values

	Age	16–25	26–35	36–45	45–55	> 55	
**Circulation**	Cardiac output	4.6–7.1	4.8–6.8	4.7–6.7	4.2–5.9	3.5–4.8	l/min

### Outcome measures

#### Primary outcome measures

The primary outcomes measures for the PREMOM II study will be: (1) prenatal follow-up data, including the numbers of prenatal consultations, ultrasounds, cardiotocograms, hospitalizations to a prenatal ward, and duration of hospitalization; (2) delivery data, including duration of labor, complications, mode of delivery, and date of delivery; (3) neonatal data, including gestational age at delivery, date and hour of delivery, APGAR, birth weight, length, complications, NICU hospitalization, and duration of hospitalization; (4) RM data, including duration of participation, number of contacts with the pregnant women regarding vital signs, number of contacts with the responsible obstetrician, numbers of prenatal consultations and hospitalizations due to RM data, and information about the interventions; and (5) compliance rates in the midwife-assisted RM and PSM groups.

#### Secondary outcome measures

Three sets of secondary outcome measures are planned: (1) cost–benefit and willingness to pay analyses to assess health economics; (2) patient-reported outcome measures (PROMs) assessed using questionnaires to document the women’s experiences; and (3) gestational outcomes in relation to administration of antihypertensive drugs.

### Data collection

Data on background variables, obstetric outcomes, and neonatal outcomes after delivery will be collected from the electronic patient files recorded at each hospital. Data on blood pressure and the associated compliance rate will be collected from DHARMA, an online platform developed by the Mobile Health Unit (Limburg Clinical Research Center, Hasselt University – ZOL - Jessa). Information about healthcare costs of pre-, peri-, and postnatal care will be collected from the Intermutualistisch Agentschap (IMA) health insurance database [41]. Information about the PROMs will be recorded using validated questionnaires.

### Sample size calculations

Sample size calculations were performed by Censtat (Hasselt University, [name], [name]) to detect clinically meaningful differences between the midwife-assisted RM group and the CG in women with GHD, for two key factors (1) gestational age for neonates born before 34 weeks and (2) admission to the prenatal ward for neonates born after 34 weeks, based on previous work.
Gestational age for neonates born before 34 weeks: a difference of ≥10 days between the midwife-assisted RM group and the CG was observed in our pilot studies, and was used as a clinically relevant difference for the power calculation. Priority was given to this sample size calculation because each 1-day increase in gestational age at birth has a significant impact on the neonate’s short- and long-term outcomesAdmission to the prenatal ward of neonates born after 34 weeks: a proportional difference of 20% between the midwife-assisted RM group and the CG was considered clinically relevant. This outcome was expected to be most frequent in the PSM group, followed by the CG group, and less likely in the RM group.

The sample size calculations are based on summary statistics derived from our pilot study. A power of 80% and a significance level of 1.67% was used. A within-center variance of 6 (for gestational age) and a random intercept standard deviation of 0.0875 (for prenatal ward admission) was assumed. To obtain 80% power, we estimated that ≥168 GHD pregnancies with delivery before the gestational age of 34 weeks and ≥ 360 GHD pregnancies admitted to the prenatal ward after 34 weeks would need to be included in the study. At each center, the women will be equally divided into the three study groups.

Based on the numbers from Studiecentrum voor Perinatale Epidemiologie (Brussels, Belgium), these 168 births before 34 weeks account for 6.6% of a total of 2545 GHD deliveries. Furthermore, GHD pregnancies represent 4.6% of the total number of pregnancies (55,335) per year [1]. As observed in prior studies, 68% of women with GHD require interventions for their GHD, we estimate a ratio of 100 to 68 pregnant women (or 1.47 to 1) will be needed for the RM group to treat one patient with GHD. As such, 6.76% (4.6% × 1.47) of these women are at risk of developing GHD, meaning 3741 women will need to be enrolled in our study. Taking into account a dropout rate of 4.83% (based on our previous studies), we will need to enroll a total of 3922 women and screen 57,998 women.

For the second sample size calculation (admission to a prenatal ward after 34 weeks), we estimated that > 360 women delivering at a gestational age later than 34 weeks will need to be enrolled across the four prenatal wards. Based on prior studies, ≥42% of women with GHD will be admitted to a prenatal ward. Therefore, out of 5931 deliveries after 34 weeks (6107 eligible women – 176 [168 + dropout rate of 4.83%] who will deliver before 34 weeks), approximately 2491 mothers will be hospitalized. As such, the sample size needed to assess this outcome is expected to be satisfied by the sample size required to show a difference in gestational age in deliveries before 34 weeks.

The primary statistical analysis will entail comparisons among the three study groups using the two-sided Fisher’s exact test at a significance level of 0.05. Adjustment for baseline variables will be performed if necessary, and interaction analyses will be performed using multivariable logistic regression analyses. The median, 95% confidence intervals, quartiles, means, and standard deviation will be calculated as appropriate.

The statistician will be blinded to the study groups.

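### 168 births give 80% power for a 1.5-week (10.5-day) difference; at the 10-day minimum that the article names, two-sided power is about 75%

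*Protocol article*

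**What the plan says.** All the inputs stand in the protocol article, under Sample size calculations.

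- **Comparison:** the calculation was made "to detect clinically meaningful differences between the midwife-assisted RM group and the CG in women with GHD". The first of its two key factors is gestational age among births before 34 weeks, which the article says was given priority.
- **Difference:** "a difference of ≥10 days between the midwife-assisted RM group and the CG was observed in our pilot studies", and this "was used as a clinically relevant difference for the power calculation".
- **Variance:** "A within-center variance of 6 (for gestational age"). No unit is printed.
- **Power and level:** "A power of 80% and a significance level of 1.67% was used". Whether this is one- or two-sided is not said.
- **Allocation:** "At each center, the women will be equally divided into the three study groups".
- **Result:** "we estimated that ≥168 GHD pregnancies with delivery before the gestational age of 34 weeks".

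The only statement on sidedness concerns the primary analysis, a "two-sided Fisher’s exact test at a significance level of 0.05". That is a different test at a different level.

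**The concern.** A reader who wants to check 168 has one printed number for the effect, 10 days. Entered with the other inputs in a standard two-sided comparison of two means, it does not return 168, and 168 births fall short of the stated 80% power. The difference is printed in days, while the variance makes sense only in weeks squared, so the reader also has to guess the unit before the check can start.

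The figure matters because the enrolment target is built on it: 168 / 6.6% gives 2545 deliveries with gestational hypertensive disorders, from which the article goes on to 55,335 pregnancies, 3741 women and, with dropout, 3922. The article itself argues that each single day of gestational age counts, so the exact difference that the trial is powered for is not a detail to its readers.

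**Working it through.** **Inputs.** From the article: variance 6, level 1.67%, power 80%, three equal arms, 168 births in total, so 168 / 3 = 56 per arm. Assumed: variance in weeks squared, and a two-sided test for the main line.

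**Unit of the variance.** If 6 were in days squared, 10 days would need 2 × 6 × 10.464 / 10² = 1.26, so 2 women per arm. Only weeks squared gives a figure near the one stated. The standard deviation is then √6 = 2.449 weeks.

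**Formula.** n per arm = 2 × variance × (z for the level + z for power)² / difference². Two-sided at 0.0167, the z values are 2.393 and 0.842, and the square of their sum is 10.464.

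**Reproducing the stated figure.** With 1.5 weeks (10.5 days): 2 × 6 × 10.464 / 1.5² = 125.57 / 2.25 = 55.8, so 56 per arm and 3 × 56 = **168**, exactly as stated.

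**At the named lower bound.** 10 days = 1.4286 weeks: 125.57 / 2.0408 = 61.5, so 62 per arm and 3 × 62 = **186**. The t distribution gives 63 per arm, 189 in total.

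**Power with 56 per arm.** The standard error of the difference is √(12/56) = 0.4629 weeks.

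- 10 days: 1.4286 / 0.4629 − 2.393 = 0.693, so power is **75.6%** (74.3% by the t distribution).
- 10.5 days: 1.5 / 0.4629 − 2.393 = 0.847, so power is 80.2% (79.0% by the t distribution).

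**Smallest difference with 80% power at 56 per arm.** 0.4629 × (2.393 + 0.842) = 1.497 weeks = 10.48 days. To keep 10 days with 56 per arm, the variance would have to be about 5.46 instead of 6.

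**Other readings of the text.**

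| Reading | Per arm | Total | Power at 168 |
|---|---|---|---|
| 10.5 days, two-sided 1.67% | 56 | 168 | 80.2% |
| 10 days, two-sided 1.67% | 62 | 186 | 75.6% |
| 10 days, one-sided 1.67% | 52 | 156 | 83.1% |
| 10 days, three-arm F test at 1.67%, self-monitoring arm equal to control | 57 | 171 | 79.3% |

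The F test comes close, but it does not give 168, and it is not the comparison that the article says it powered, which is remote monitoring against control. A level of 1.67% = 5% / 3 also points to pairwise tests. With the self-monitoring arm halfway between the other two, the same F test would have 64.1% power.

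**The case against.** The strongest reply is that the article does not say 10 days; it says 10 days or more. A value of 10.5 days satisfies that, and with the other inputs it returns 168 to the unit. This suggests a sound calculation loosely described in a condensed article, not an error of arithmetic. In addition, the variance unit and the sidedness have to be supplied by whoever checks the figure, and with a one-sided test at exactly 10 days 168 is more than enough.

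Most of this stands. A reader might infer that the stated inputs require 186 births, that 168 is therefore wrong, and that the enrolment target must rise in the ratio 186 / 168. The documents do not support that. It would follow only if exactly 10 days, tested two-sided, was the target, and the text fixes neither. If 1.5 weeks was entered, nothing in the chain from 168 to 3922 changes.

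What does not stand is that the lower-bound wording disposes of the matter. A target written as a minimum names that minimum as the smallest effect to be detected, and a statement of 80% power should hold there. Under the two-sided pairwise reading that reproduces 168, it does not. A one-sided test does not explain the figure either: it leads to 156 at 10 days, not 168.

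**Conclusion.** The point holds as a mismatch between the printed effect and the printed power. The 168 births correspond to 80% power for 1.5 weeks (10.5 days). At the 10 days that the text names as its minimum, the same inputs give about 75% power, and 80% would take about 186 births. The size is modest: half a day in the effect, or about five percentage points of power.

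This rests on two assumptions that the article does not state: variance in weeks squared, for which the implausible alternative is strong support, and a two-sided test, which the exact match at 1.5 weeks supports but does not prove. If the test was one-sided, 168 gives 83% power at 10 days and the shortfall disappears. That 1.5 weeks was the value entered is an inference from the match. The finding does not show that enrolment is too small.

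**What to change.** Keep 168 and reword the sentence so that effect and power agree. Either state 80% power for a difference of 1.5 weeks (10.5 days), or state about 75% power for a difference of 10 days. In the same sentence, give the difference as one exact value, print the unit of the variance (weeks squared), and say that the 1.67% test is two-sided, once the sponsor has confirmed all three against the calculation that was run.

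The cost is one sentence. The stated effect or power becomes slightly less favourable; no patients are added and the enrolment target of 3922 stays as it is.

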### Study design

PREMOM II is a multicenter, randomized controlled trial that will be performed at five hospitals with their own prenatal wards between October 1, 2018 and March 30, 2022. The centers combined will perform more than 7000 deliveries per year. Eligible participants will be pregnant women ≥18 years old, who are able to understand oral and written information, with a minimum risk of 1/100 on the Fetal Medicine Foundation Tool (FMF) [28, 29]. By using the FMF tool will a risk assessment for the development of early PE be made, in which the following parameters are taken into account: (1) maternal characteristics; (2) medical history; (3) obstetric history; (4) information about the current pregnancy; (5) biophysical measurements. Women will be excluded if a congenital malformation is detected or if they do not have a smartphone.

The ethics committee at Universitair Ziekenhuis Antwerpen (UZA; Wilrijk) approved the study in July 2019 (Belgium Registration Number: BE300201938651). The local ethics committees at ZOL, Universiteit Ziekenhuis Leuven (Leuven), AZ Sint Jan (Bruges), and AZ Sint Lucas (Bruges) provided advice to the ethics committee at UZA before the study was approved.

General information about the study will be available at the antenatal care units at each site. All women who are pregnant for the first time, or who had a history of GHD in previous pregnancies, are given oral and written information about the study when they undergo their first trimester ultrasound examination. They will also be asked whether they want to be screened for the development of early PE. Women who are interested in participating the study are asked to give their informed consent and their risk will be calculated using the FMF tool. Pregnant women with a risk < 1/100 will not be randomized in the study, but will receive the standard follow-up in accordance with the local routine care. Pregnant women with a risk ≥1/100 will be randomized in one of the three study groups.

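### The enrolment target of 3741 (3922 with dropout) has no valid basis for yielding 168 GHD births before 34 weeks, because the 68% behind it is defined on one group of women and applied to another

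*Protocol article*

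**What the plan says.** All of this is in the protocol article.

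- **Sample size calculations, births needed.** The priority calculation asks for "≥168 GHD pregnancies with delivery before the gestational age of 34 weeks". The effect is described as "a difference of ≥10 days between the midwife-assisted RM group and the CG was observed in our pilot studies", and the error rates as "A power of 80% and a significance level of 1.67% was used".
- **Sample size calculations, from births to GHD deliveries.** "these 168 births before 34 weeks account for 6.6% of a total of 2545 GHD deliveries". GHD is put at 4.6% of 55,335 pregnancies.
- **Sample size calculations, from GHD deliveries to enrolment.** "68% of women with GHD require interventions for their GHD, we estimate a ratio of 100 to 68 pregnant women (or 1.47 to 1". The prevalence is then multiplied by this ratio: "6.76% (4.6% × 1.47) of these women are at risk of developing GHD, meaning 3741 women will need to be enrolled in our study". A dropout rate of 4.83% raises the figure to 3922.
- **Study design, who is enrolled.** Eligible women are those "with a minimum risk of 1/100 on the Fetal Medicine Foundation Tool (FMF", a tool that the section says assesses the risk of early pre-eclampsia. "Pregnant women with a risk ≥1/100 will be randomized in one of the three study groups".

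**The concern.** To turn a required number of GHD deliveries into a number to enrol, one needs the proportion of enrolled women who will develop GHD. The 68% is described as something else: the proportion needing intervention among women who have GHD. That rate cannot convert GHD cases into women at risk of GHD.

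The entry rule does not supply the missing link. Women are selected at 11 to 14 weeks by a predicted-risk threshold for early pre-eclampsia. Neither the 68% nor the 6.76% is tied to that threshold.

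The section gives this calculation priority and relies on it to cover the second key outcome, admission to the prenatal ward. The headline enrolment in the abstract, and the 80% power for gestational age among births before 34 weeks, depend on an unsupported step.

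**Working it through.** **1. Reproduce the plan's figures** (all inputs from Sample size calculations).

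- GHD deliveries: 168 / 0.066 = 2545
- Pregnancies: 168 / 0.066 / 0.046 = 55,336 (stated 55,335)
- Ratio: 1 / 0.68 = 1.47
- At-risk share: 4.6% × 1.47 = 6.76%
- Enrolment: 2545 × 1.47 = 3741
- With dropout: 3741 × 1.0483 = 3922

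The arithmetic reproduces throughout. The problem is the meaning of one input.

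**2. What the chain assumes.**

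- Share of enrolled women who develop GHD: 2545 / 3741 = 68%.
- Share of enrolled women with a GHD birth before 34 weeks: 168 / 3741 = 4.5%.
- Capture of cases: 3741 × 0.68 = 2544, against 55,335 × 0.046 = 2545 GHD cases in the whole population. The selected 6.76% would have to contain every GHD case.

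The article supports none of the three for women at or above the 1/100 threshold.

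**3. Does a literal reading of the 68% help?** If only GHD women needing intervention were meant to count, then 2545 / 0.68 = 3741 would be the number of women *with* GHD. Enrolment of at-risk women would have to be larger still.

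**4. What would still give 168 births.** Let p be the share of enrolled women who develop GHD and e the share of those delivering before 34 weeks. Then births = 3741 × p × e, and the e required is 168 / (3741 × p).

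| p | e required for 168 births |
|---|---|
| 68% | 6.6% |
| 50% | 9.0% |
| 30% | 15.0% |
| 20% | 22.5% |

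**5. Illustrative yield and power.** Assumptions: e held at 6.6%; births split equally over three groups; two-sample t test of a 10-day difference; alpha 0.0167, taken as two-sided (the article does not say). The SD is calibrated to about 16.1 days so that 56 births per group (168 in all) give the plan's own 80%. The values of p are assumed, since the article gives none.

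| p (assumed) | Births before 34 weeks | Power |
|---|---|---|
| 68% | 168 | 80% |
| 50% | 123 | 64% |
| 40% | 99 | 53% |
| 30% | 74 | 39% |
| 20% | 49 | 24% |
| 10% | 25 | 11% |

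For example, at p = 40%: 3741 × 0.40 × 0.066 = 99 births, or 33 per group.

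**6. The second calculation offers no independent support.** It takes a share of at least 42%, again described for women with GHD, and applies it to all 5931 remaining eligible women: 5931 × 0.42 = 2491. This is the same change of denominator.

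**The case against.** The strongest reply is that the 68% comes from the group's earlier studies, which the Background describes as comparing women at elevated risk of GHD. The phrase about treating one patient with GHD could be a poorly worded figure for at-risk women who went on to need treatment. In that case the number might be usable and only its description wrong. This stands in part: the article shows an inconsistent denominator, but not which side of it is the mistake. Even so, the figure would still have to be shown to apply to women selected by the present entry rule, and nothing in the article does so.

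A reader might infer more: that enrolling 3922 women *will not* yield 168 births. The article does not support that. It gives no GHD incidence and no early-delivery share for the selected cohort. Because selection is on predicted early pre-eclampsia, the early share may well exceed the population's 6.6%, and the combinations in step 4 would still reach 168.

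A reader might also take the 1/100 threshold to mean that about 1% of enrolled women will have an early birth, or 37 of 3741. That does not follow either. The threshold is the lowest risk admitted, not the average, and early pre-eclampsia is not the same event as a GHD delivery before 34 weeks.

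Nor is this a detail that an article leaves to a fuller document. The derivation is published, and the published step does not follow.

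**Conclusion.** The point holds in this form: the target of 3741, or 3922 with dropout, has no valid stated basis for yielding 168 GHD births before 34 weeks. The denominator inconsistency is certain from the text. So is the implied requirement of about 4.5% of enrolled women having such a birth.

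Whether there will be a shortfall, and how large, cannot be settled from the article. The power figures show sensitivity and are not predictions. They rest on assumed incidences, an early share fixed at 6.6%, a two-sided alpha and an SD calibrated to the stated 80%. Within those assumptions, power drops from 80% to 64% at an incidence of 50%, and to 24% at 20%.

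**What to change.** State the source and denominator of the 68%, and correct its description or its use. If it is not the GHD incidence among women with a predicted risk of at least 1/100, remove the 1.47 factor and replace it with two figures:

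- the GHD incidence among participants;
- the share of their GHD births that occur before 34 weeks.

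The Status section says recruitment began in September 2019 and is ongoing, so both can come from a pooled, arm-blind count among participants who have delivered. The count should be limited to women enrolled long enough ago that all should have delivered; otherwise early births are over-represented. Then restate the expected number of GHD births before 34 weeks, and the power, at 3922 across a stated range.

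The cost is one blinded count and revised sample size text. The stated power may become less favourable. No extra enrolment is proposed. If the sponsor chose instead to hold 168 births at a 6.6% early share, the number needed before dropout would be 2545.45 / p: 5,091 at an incidence of 50% and 8,485 at 30%.

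### The 4.83% dropout allowance is added to the required number instead of being divided out, so the stated enrolment of 3922 leaves about 8 women fewer than the plan's own 3741

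*Protocol article*

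**What the plan says.** Under 'Sample size calculations', the protocol article bases the power for its first key factor, gestational age for neonates born before 34 weeks, on a minimum count: "we estimated that ≥168 GHD pregnancies with delivery before the gestational age of 34 weeks". That count is scaled up to all GHD deliveries ("these 168 births before 34 weeks account for 6.6% of a total of 2545 GHD deliveries"), and then by 1.47 to women at risk, "meaning 3741 women will need to be enrolled in our study". The dropout allowance follows: "Taking into account a dropout rate of 4.83% (based on our previous studies), we will need to enroll a total of 3922 women", with 57,998 women to be screened. The 4.83% is attributed to the team's previous studies.

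The second calculation, on prenatal ward admission after 34 weeks, shows how the allowance was formed: "176 [168 + dropout rate of 4.83%] who will deliver before 34 weeks". The abstract repeats 3922 as the number of women to be randomized.

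**The concern.** A dropout rate normally means the share of enrolled participants who are lost. To end with n after losing a share d, one must enrol n/(1 − d). Enrolling n × (1 + d) always falls a little short, because the loss applies to the larger enrolled number. The bracketed expression for 176, and the size of 3922 itself, suggest that the plan used the second formula. At stake is whether the headline enrolment figure, given in both the abstract and the sample size section, delivers the number that the plan says it needs.

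**Working it through.** **Inputs, all from 'Sample size calculations'.** Births required before 34 weeks: 168. Share of GHD deliveries before 34 weeks: 6.6%. GHD prevalence: 4.6%. At-risk multiplier: 1.47 (from 100 to 68). Dropout rate d = 4.83%, so 1 + d = 1.0483 and 1 − d = 0.9517. Power 80%, significance level 1.67%.

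**Step 1: reproduce the base figure.**
- GHD deliveries: 168/0.066 = 2545.
- Women at risk: 2545 × 1.47 = 3741.

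Both match the article.

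**Step 2: find the dropout formula used.**

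| Figure | Base | Base × 1.0483 | Base / 0.9517 | Printed |
|---|---|---|---|---|
| Enrolment | 3741 | 3921.7 | 3930.9 | 3922 |
| Screening | 2545/0.046 = 55,326 | 57,998 | 58,134 | 57,998 |
| Births before 34 weeks | 168 | 176.1 | 176.5 | 176 |

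Multiplication reproduces all three printed figures. For enrolment and screening, division clearly does not. The screening figure matches only from the unrounded chain (55,326). The article also prints "GHD pregnancies represent 4.6% of the total number of pregnancies (55,335) per year", and 55,335 × 1.0483 would give 58,008.

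**Step 3: apply the stated loss to the stated enrolment.**
- Women remaining: 3922 × 0.9517 = 3732.6, about 8 below 3741.
- Expected births before 34 weeks: 3732.6 × 0.68 × 0.066 = 167.5. Scaling in proportion instead, 168 × 3732.6/3741 = 167.6. Either way the result is about half a birth or less below 168.
- Check of the alternative: 3931 × 0.9517 = 3741.1, which meets the need.
- Dropout that 3922 can absorb: 1 − 3741/3922 = 4.6% of those enrolled, against the 4.83% stated.

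**Step 4: gauge the effect on power.** Assume that 168 births (56 per group) give exactly 80% power for a two-sided comparison of two groups at 1.67%, ignoring centre effects. The standardized signal is then 2.393 + 0.842 = 3.235. With 167.5 births it becomes 3.235 × √(167.5/168) = 3.230, and power is Φ(3.230 − 2.393) = Φ(0.837) = 79.9%. The loss is roughly 0.1 percentage point.

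**Step 5: see whether the choice of 176 or 177 matters.** The article subtracts 176 from 6107 to get 5931, and takes 42% of that as 2491. With 177: 5930 × 0.42 = 2490.6, which still rounds to 2491.

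**The case against.** The strongest reply is that the correction is smaller than the imprecision of the inputs. If 6.6% stands for anything between 6.55% and 6.65%, the base runs from 168/0.0665 × 1.47 = 3714 to 168/0.0655 × 1.47 = 3770, which dwarfs a gap of 9 women. The number of early births is also random: on a Poisson assumption its standard deviation is √168, about 13, so neither 3922 nor 3931 guarantees 168. Both statements are right, and they fix the importance of the point as minor. They do not make the formula correct: given the plan's own inputs, 3922 does not return 3741.

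A second reply is that the article discloses its convention by writing the allowance as an addition, and that the denominator of the 4.83% cannot be checked because the previous studies are not shown. If the rate were dropouts per completer, multiplication would be right. Nothing in the article says so, and the usual reading is a share of those enrolled.

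Two stronger readings are tempting. A reader might infer that the trial is underpowered because of this slip; a loss of about 0.1 percentage point does not support that. A reader might also count 176 as a second error. The two formulas give 176.1 and 176.5, so the difference is a matter of rounding and no downstream figure changes. The bracket is useful only as evidence of the method.

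**Conclusion.** The point stands as a minor arithmetic correction. On the ordinary reading of a dropout rate, the enrolment figure is 9 women (0.23%) too low: it leaves about 3733 women against the stated need of 3741, and about 167.5 expected births before 34 weeks against 168. The power effect of roughly 0.1 percentage point rests on the assumption that 168 births, split equally over three groups, give exactly 80%. No design decision, analysis or conclusion depends on it. The check takes 3741 as given and covers only the dropout step. It does not validate the rest of the section's chain, including the 6107 eligible women used in the second calculation.

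**What to change.** Take one of two routes:

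- Keep 3922 and add a sentence saying that, after 4.83% dropout, it leaves about 3733 evaluable women and about 167.5 expected births before 34 weeks.
- Restate enrolment as 3931 (3741/0.9517) in the sample size section and the abstract, and screening as about 58,134 (55,326/0.9517) instead of 57,998. If the printed 55,335 is the intended base, screening becomes 55,335/0.9517 = 58,143.

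If 4.83% was in fact measured per completer, saying so would settle the matter with no change of figures. The 176 can stay. The first route costs one sentence. The second changes stated figures and adds 9 women to enrolment and about 136 to screening (58,134 − 57,998).

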## Status of the study

Recruitment started on September 1, 2019, and enrollment will continue until September 1, 2022. After this time, follow-up will continue for 6 months. The study is at this moment ongoing, patient recruitment is not yet completed at the moment of submission of this manuscript. No other publications containing the results of this study have already published or submitted to any other journal.

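### The five centres' stated delivery volume supplies about 21,000 of the 57,998 women to be screened, so about 64 rather than 168 qualifying births are expected and the 80% power is not delivered

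*Protocol article*

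**What the plan says.** The section Sample size calculations gives priority to gestational age at birth among neonates born before 34 weeks. It asks for "≥168 GHD pregnancies with delivery before the gestational age of 34 weeks" to reach 80% power at a significance level of 1.67%.

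It then works back to the number of women needed. First, "these 168 births before 34 weeks account for 6.6% of a total of 2545 GHD deliveries". Next, "GHD pregnancies represent 4.6% of the total number of pregnancies (55,335) per year". A multiplier of 1.47 then gives "6.76% (4.6% × 1.47) of these women are at risk of developing GHD", hence 3,741 women. After a 4.83% dropout allowance, "we will need to enroll a total of 3922 women and screen 57,998 women".

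On supply, Study design says: "The centers combined will perform more than 7000 deliveries per year". Status of the study says: "Recruitment started on September 1, 2019, and enrollment will continue until September 1, 2022". Study design gives a different period for the trial, "between October 1, 2018 and March 30, 2022". The article nowhere compares the screening number with the centres' volume.

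**The concern.** The plan derives the population it needs but does not check it against the population it has. The 55,335 pregnancies in the calculation carry a per-year label and are close to the 64,000 yearly pregnancies that the Background gives for all of Flanders. The five centres handle a fraction of that.

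If the centres cannot supply the women, then 3,922 enrolled, 168 qualifying births and 80% power do not describe this trial. The comparison that sets the sample size would run at well under half the stated power, and a non-significant result could be read as coming from an adequately powered trial.

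**Working it through.** **Inputs from the article.** Qualifying births needed: 168. Share of GHD deliveries before 34 weeks: 6.6%. GHD prevalence: 4.6%. At-risk share: 6.76%. Dropout: 4.83%. Deliveries: 7,000 a year, a floor. Enrolment: 1 September 2019 to 1 September 2022, 3 years. Alpha 0.0167, power 80%, difference at least 10 days, within-centre variance 6, three equal arms.

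**Inputs I had to assume.** The variance is in weeks squared (no units are given), so SD = √6 = 2.449 weeks. The sample size test is two-sided (the article says so only for the analysis).

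**1. Reproduce 168.** n per arm = 2 × 6 × (2.394 + 0.842)² / δ².
- δ = 1.5 weeks: 56 per arm, × 3 = 168. This matches.
- δ = 10/7 weeks (exactly 10 days): 62 per arm, × 3 = 186. This does not match.

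The plan's figure therefore fits 10 days rounded up to 1.5 weeks, with a normal approximation.

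**2. Reproduce the screening chain.** 168 / 0.066 = 2,545. 2,545 / 0.046 ≈ 55,330. 2,545 × 1.47 = 3,741. 3,741 × 1.0483 = 3,922. 3,922 / (0.046 × 1.47) ≈ 58,001, against 57,998 stated. The chain is reproduced to within rounding.

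**3. Supply.** 7,000 × 3 = 21,000, and 21,000 / 57,998 = 36%. Conversely, 57,998 / 7,000 = 8.3 years, or 57,998 / 3 ≈ 19,300 deliveries a year for a three-year window.

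**4. Run the plan's rates forward.**
- Enrolled: 21,000 × 0.0676 ≈ 1,420, or 36% of 3,922.
- Qualifying births: 21,000 × 0.046 × 0.066 = 63.8, about 64, or 21 per arm. After 4.83% dropout, about 61.
- Cross-check from the Background (about 200 such births a year among 64,000 pregnancies): 200 × 3 × 7,000 / 64,000 ≈ 66.

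**5. Power at that count.** Noncentrality = δ / (2.449 × √(2/n)), with n = births / 3 per arm.

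| Basis | 168 births | 64 births |
|---|---|---|
| 1.5 weeks, normal | 80% | 35% |
| 1.5 weeks, t-test | 79% | 32% |
| 10 days, normal | 76% | 31% |
| 10 days, t-test | 74% | 29% |

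Scaling directly from 80% at 168 births gives Φ(3.236 × √(63.8/168) − 2.394) = 34%.

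**6. Detectable difference at 64 births, 80% power.** 3.236 × 2.449 × √(2/21.25) = 2.43 weeks = 17.0 days (normal approximation); 17.6 days with the t-test.

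**7. Range.**
- Whole 3.5-year period from Study design: 24,500 women, about 74 births, power 38–41% (1.5 weeks) or 34–37% (10 days).
- 8,000 deliveries a year for 3 years: 24,000 women, about 73 births, power 37–40% (1.5 weeks) or 34–36% (10 days).
- Enrichment needed to reach 168 births: 168 / 63.8 ≈ 2.6-fold.

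**The case against.** The best defence is that 64 is an expectation and not a ceiling. The delivery figure is a floor, the rates come from a regional register, and the centres include university hospitals whose rates of GHD and early birth the article does not give. That is right, and a reader should not infer that the count cannot exceed 64. But 8,000 deliveries a year adds only about nine births, and the article neither states nor assumes enrichment near 2.6-fold. Randomization at 11 to 14 weeks also means that women transferred in later with established disease cannot be enrolled. Other features push the count down: only first pregnancies and women with previous GHD are approached, and consent, a smartphone and a risk of at least 1/100 are required.

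A reader might also sum the problem up as 29% power instead of 80%. That mixes two bases. The 29% comes from exactly 10 days and a t-test, on which 168 births give only 74%. Some of that gap therefore comes from the change of effect size and method, and not from the shortage of women.

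A third tempting step is to demand a different lead endpoint, such as prenatal ward admission. The documents do not require it. Priority is given to a sample size calculation and no single lead endpoint is named, while ward hospitalization is already among the primary outcomes. Nor would a null result be worthless: low power widens the interval, and the trial has many other primary outcomes.

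Finally, the dates in Study design cover the conduct of the trial and not recruitment alone, so the 3.5-year figure is a generous sensitivity case and not a like-for-like recruitment pool.

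**Conclusion.** The point stands as an internal contradiction. The stated volume and enrolment period yield about 36% of the women the calculation says must be screened, and nothing in the article closes the gap. At the plan's own rates about 1,420 women would be enrolled and about 64 qualifying births expected (about 74 over 3.5 years).

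Power for the prioritised comparison is then about 32–35% on the basis that gives the plan its 80%, or 29–31% with exactly 10 days. None of the variants examined comes near 80%. The mismatch in supply is firm, as it needs only the article's own figures. The power figures also rest on reading the variance as weeks squared, a two-sided alpha of 0.0167, complete screening and consent, and no referral enrichment.

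**What to change.** 1. Reconcile the dates in Study design with those in Status of the study, and state one recruitment period.
2. Replace 3,922 enrolled, 57,998 screened, 168 births and 80% power with the enrolment the five centres can reach in that period.
3. At that size, state the expected number of GHD births before 34 weeks and the power or detectable difference. Give the assumptions: delivery volume, proportion approached and consenting, event rates and any referral enrichment with its source, effect size, and the units of the variance.
4. Stop describing gestational age before 34 weeks as an 80%-powered comparison.

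This costs a rewritten paragraph and an amendment to the stated figures. It needs no extra participants and no change of lead endpoint. The stated power becomes less favourable.
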